### Ethics Approval

This research will be conducted in accordance with the Declaration of Helsinki. The study was approved by the Scientific Ethics Committee of the Aconcagua Health Service (protocol number: 26/2021, approved October 12, 2021) and the Scientific Ethics Committees of the South Metropolitan Health Service (protocol number: 07-27012022, approved February 7, 2022). Informed consent will be obtained from all participants invited to participate in the study before proceeding with the initial survey. The data will be treated respecting the ethical principles that guarantee the anonymity of the participants.

## Results

The study was funded by the National Research and Development Agency of Chile in December 2021. The data collection began on May 2, 2022. Study staff have been engaged in activities associated with study including enrollment and data collection. As of November 30, 2022, a total of 222 pregnant women have been admitted for the first prenatal appointment, 127 meet the inclusion criteria, and 76 agree to participate and answered the diagnostic survey. The expected timeframe for completing recruitment and data analysis is November 2023.

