**Results:**

The recruitment of study participants began in May 2022 and will end in May 2023. Results include the effectiveness of the intervention in reducing the incidence of excessive gestational weight gain. We also will examine the maternal-fetal outcome as well as the barriers and facilitators that influence the weight gain of pregnant women.

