### Sample Size Calculation

The total sample consists of 511 participants, which will be divided into 2 groups. In the El Bosque CESFAM, 280 pregnant women were recruited, with an estimated dropout rate of 30% (based on the pilot study carried out) to guarantee the required sample size of 210 pregnant women with a confidence level of 90% and a 5% error. At Segismundo Iturra CESFAM, 231 pregnant women were recruited, with the same estimated dropout rate, to ensure a sample size of 178 pregnant women with a confidence level of 90% and a 5% error. For the calculation of the sample size, the official records of the DEIS regarding the number of pregnant women between 20 and 44 years of age who were treated for prenatal control in the CESFAM of the El Bosque commune and Segismundo Iturra were considered. The recruitment period will be 6 months.

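### The target of 511 women does not fit any of the three recruitment end dates in the article, given its own count of 76 participants after seven months

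*Protocol article*

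**What the plan says.** All statements are in the protocol article.

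- Size (Sample Size Calculation): "The total sample consists of 511 participants, which will be divided into 2 groups". The parts are written as accomplished: "In the El Bosque CESFAM, 280 pregnant women were recruited, with an estimated dropout rate of 30" per cent, and "At Segismundo Iturra CESFAM, 231 pregnant women were recruited, with the same estimated dropout rate".
- Window (same section): "The recruitment period will be 6 months". Procedures repeats 6 months.
- Second end date (abstract, Results): "The recruitment of study participants began in May 2022 and will end in May 2023".
- Third end date (Results): recruitment and data analysis are expected to be complete in November 2023.
- Actual accrual (Results): data collection began on 2 May 2022. By 30 November 2022, 222 women had been admitted for a first prenatal appointment, and of these "127 meet the inclusion criteria, and 76 agree to participate and answered the diagnostic survey".
- Use of the size (Statistical Analysis): every randomised woman is analysed, dropouts count as treatment failures, and effectiveness is to be confirmed by a two-sided P<.001.

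**The concern.** The section that sets the size and the section that reports progress cannot both be right. One describes 511 women as recruited and gives 6 months for recruitment. The other, written after those 6 months had passed, counts 76. The article also gives three different ends for recruitment, so a reader cannot tell which size goes with which date.

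The size determines what the primary comparison can show. The test is presented as confirming effectiveness, and the Discussion looks ahead to prevention strategy and public policy. If the trial closes well short of 511 while the article still carries that figure, a non-significant result may be read as absence of effect when the trial had little chance of detecting any but a very large one.

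**Working it through.** **1. The stated figure.** 280 + 231 = 511, so the sum is correct. The required numbers behind it are 210 + 178 = 388. The problem is consistency between size, dates and count.

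**2. The 6-month window.** Six months from 2 May 2022 ends about 2 November 2022. Four weeks later the count was 76.
- 76 / 511 = 14.9%.
- Counting all eligible women: 127 / 511 = 24.9%.
- Rate needed for 511 in 6 months: 511 / 6 = 85 a month.

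This step uses reported counts only.

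**3. Observed rates.** 2 May to 30 November 2022 is 212 days, or 212 / 30.44 = 6.97 months.
- Agreed and answered the survey: 76 / 6.97 = 10.9 a month.
- Eligible: 127 / 6.97 = 18.2 a month.
- All first-visit admissions: 222 / 6.97 = 31.9 a month.

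**4. Projection, assuming constant intake.** Total = 76 + monthly rate × months remaining after 30 November 2022 (4.99 to 1 May 2023, 5.98 to 31 May 2023, 11.99 to 30 November 2023).

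| Assumption from December 2022 | 1 May 2023 | 31 May 2023 | 30 Nov 2023 |
|---|---|---|---|
| Observed rate, 10.9 a month | 130 | 141 | 207 |
| Every eligible woman joins, 18.2 a month | 167 | 185 | 295 |
| Every admitted woman joins, 31.9 a month | 235 | 267 | 458 |

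Taking the upper 95% Poisson limit on the count of 76 (95.1) as the rate throughout gives 177 by 31 May 2023 and 259 by 30 November 2023.

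The shortfall is 511 − 76 = 435 women. Closing it needs:
- 435 / 4.99 = 87 a month to 1 May 2023, or 435 / 5.98 = 73 a month to 31 May 2023 (8.0 and 6.7 times the observed rate);
- 435 / 11.99 = 36 a month to 30 November 2023 (3.3 times).

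Each exceeds the 31.9 a month at which all women, eligible or not, were admitted. At 10.9 a month, 511 takes 511 / 10.9 = about 47 months.

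**5. Consequence for the comparison.** The article gives no control rate of excessive weight gain, so 40-50% is an assumption. For n per arm and 80% power, the smallest detectable reduction d = p1 − p2 solves

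d√n = z(1−α/2) √[2p̄(1−p̄)] + 0.842 √[p1(1−p1) + p2(1−p2)],

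with p̄ = (p1 + p2)/2 and z = 1.960 for .05 or 3.291 for .001. Example: n = 71, p1 = 0.50, p2 = 0.176, so p̄ = 0.338. The right side is 3.291 × 0.669 + 0.842 × 0.629 = 2.73, and 2.73 / √71 = 0.324.

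| Women randomised (per arm) | d at P<.001 | d at .05 | 95% CI half-width, 1.96√(0.5/n) |
|---|---|---|---|
| 511 (255) | 17-18 points | 12 points | 9 points |
| 207 (104) | 25-27 points | 18-19 points | 14 points |
| 141 (71) | 30-32 points | 21-23 points | 16 points |

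The half-width formula takes both proportions as 50%, which is the widest case.

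**The case against.** The strongest reply has several parts.

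*The past tense is a slip.* Probably so: the same section uses the future tense elsewhere, and Results reports the true count openly. A reader might infer that the article claims 511 women are enrolled, but read as a whole it does not support that. Correcting the tense does not reconcile the size with the dates.

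*The later dates rest on extrapolation.* This stands. The 6-month miss is a fact, but a shortfall in May or November 2023 assumes that intake stays constant. The article does not say when each of the seven centres opened. A reader might infer that 511 is impossible. The documents support only that it is out of reach unless intake rises above all admissions so far, and they mention no added centres or change in recruitment.

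*76 may not be the number randomised.* This also stands. The count is of women who agreed and answered the survey. Randomization and Masking places the survey before randomisation, while Procedures sends the link after it. If Procedures is right, non-responders are already randomised and 10.9 a month is too low. The limit of 127 eligible women still leaves the 6-month conflict intact.

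*Low sensitivity is not due to accrual alone.* Correct. Even with 511 women, the P<.001 threshold requires a 17-18 point reduction. The size was also set from a confidence level and an error margin at each site, as in "to guarantee the required sample size of 210 pregnant women with a confidence level of 90% and a 5% error", and not from the power of the comparison. Those are separate matters. Accrual adds to them, as the table shows.

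**Conclusion.** The point holds as an inconsistency between stated size, stated dates and reported count. The 6-month window closed with at most 15% of 511 (25% if all eligible women are counted), and two other end dates appear without reconciliation. That part rests on no assumption.

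Under constant intake, 511 is about 3.9 times what 1 May 2023 would deliver (511 / 130) and about 2.5 times what 30 November 2023 would deliver (511 / 207). The second multiple is the most favourable, because the November date also has to cover data analysis. No single multiple is justified while three end dates stand. The detectable differences further assume a 40-50% control rate, 80% power and equal arms.

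A reader might go on to apply the 30% dropout and conclude that only about 100 women would be analysed by May 2023. The Statistical Analysis section does not support this, because it analyses every randomised woman and counts dropouts as failures. A reader might also infer that the primary result must be recast as estimation only. That is a choice for the sponsor and does not follow from the inconsistency.

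**What to change.** 1. Reconcile the three ends of recruitment (6 months, May 2023, November 2023) in the abstract, Sample Size Calculation, Procedures and Results.
2. Describe 280 and 231 as planned numbers.
3. State one consistent pair: either a size attainable by the chosen date, or the target of 511 with a realistic later date. Report the number randomised separately from the number who answered the survey.
4. For the restated number randomised, give the expected CI width or the detectable difference at the plan's own threshold, with the assumed control rate, so that a null result is not read as absence of effect.

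The cost is a less favourable stated size or a later end date. The restatement itself is wording plus one short calculation and requires no extra patients.

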## Discussion

### Principal Findings

It is well known that pregestational obesity has been recognized as a risk factor for several perinatal complications, such as fetal macrosomia, gestational diabetes, hypertensive disorders, failed induction, premature rupture of membranes, and cesarean section [38]. Nevertheless, this risk is increased when eGWG is present [39,40]. Prevention strategies in primary care are key to fighting this problem; in this regard, strategies that target behavior change by promoting self-efficacy have been proposed [37]. A recent study conducted focus groups with 66 women between 16 and 24 weeks’ gestation [19], and the participants expressed that the difficulties in operationalizing the information in the guidelines and that provided by health care providers were one of the important barriers to self-care. For this reason, care providers’ advice on nutrition and physical activity was perceived as minimal and ineffective. We propose the integration of social cognitive theory with mHealth to provide nutritional information to pregnant women in primary care. In this study, the structure of the messages addresses 3 learning domains (cognitive, affective, and psychomotor) that promote self-efficacy [37]. The hypothesis of this study is that the mHealth intervention called mami-educ is effective in reducing eGWG in pregnant women who attend family health care centers in an urban area and another predominant rural area. From a public policy perspective, effective health communication is very important; mHealth provides fast, easy-to-use, and cost-effective communication. We designed this study to address the gap in evidence-based primary prevention strategies regarding the use of mHealth to reduce eGWG. Overall, this proposal has the potential to reduce the incidence of perinatal complications through adequate gestational weight gain. To ensure the reproducibility of the study for future research and reduce the risk of comparability bias, the design of the intervention corresponds to a classic RCT. This design allows us to carry out a prospective study of pregnant women in which it is intended to compare the effect of the intervention versus the control condition to establish a cause-and-effect relationship.

The results of this study may serve to implement evidence-based primary prevention strategies and help a broader group of pregnant women maintain adequate weight gain during pregnancy and prevent pregnancy pathologies associated with obesity. This would ultimately influence health care costs. In Chile, it has been described that the cost of overweight and obesity increases to US $455 million by year, representing 2% of the total health budget, which means that obesity costs 4-fold higher than normal weight health care [41]. Through this observation, the projected health costs for 2030 related to overweight and obesity will reach 3.4% of the total health budget (US $3 billion). Furthermore, it is estimated that a weight reduction of 7%-10% in the obese population would translate into a 40% decrease in spending on obesity-associated comorbidities [42]. Thus, promoting adequate weight gain during pregnancy in women with obesity could improve maternal, fetal, newborn, and offspring health and could significantly reduce public health care costs. Lastly, the data collected in this study can play a central role in the development of public policies based on mHealth directed exclusively to the population of pregnant women.

### Limitations

A limitation of this study is the reliance on smartphones to access interventions. In addition, the recruitment of pregnant women must occur during the first trimester of gestation, and this may be hindered because some pregnant women begin prenatal care in the second trimester. Another limitation is that the pregnant woman may decide not to interact with the messages by blocking the number of the intervention.

## Appendix

Multimedia Appendix 1 Evaluation report.

## Abbreviations

CESFAM: Centro de Salud Familiar
eGWG: excessive gestational weight gain
mHealth: mobile health
MMS: multimedia messaging system
RCT: randomized controlled trial
